### Protocol optionality

2.2

Participation in the questionnaire aspect of the programme is offered to all staff in participating organizations, regardless of their original working schedule (e.g., part-time status, compressed hours, etc.). However, participation in any additional remote (see Section 2.9) or in-person measures (see Section 2.10) is offered only to those working full-time at the start of the study period, due to limited resources for acquiring specific types of data (e.g., MRI scanning costs, sleep-watch availability). Therefore, everyone, regardless of working pattern, completes the questionnaires, and full-time staff have the option to volunteer for additional remote or in-person measures

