## Abstract

Long working hours can negatively affect workers' health, wellbeing, and work performance. Previous trials reducing working time have found improvements in multiple aspects of wellbeing, including sleep, job satisfaction, and reduced burnout, while maintaining performance. However, the potential psychological and biological mechanisms underlying these improvements, including immune function and brain function, remain unexplored. Therefore, the aim of this study is to understand the bidirectional relationship between working patterns and physical and mental health, and how workplace performance is affected. We aim to test at least 150 working-age adults in the UK (approximately half with a working time reduction and no loss of salary, and half controls with no change in working patterns) in a 14-week trial, including a 2-week baseline period, with additional participants completing questionnaires only. The primary outcome measure is the difference in physical and mental health from baseline to the end of the trial among participants undergoing a reduction in working time, compared with the control group. Data collection is currently underway, and while the majority of employers in the working time reduction group adopt a 4-day week format, the specific change in working patterns is flexible and varies between employers according to their operational need, including a 9-day fortnight, two half-days and shorter working days. Core variables include brain structure and function, sleep, immune function, interoception (perception of bodily sensations), time use, diet, mental health, and workplace performance and engagement. Secondary outcomes include weekly monitoring of self-reported wellbeing changes to identify key inflection points and assess whether these are maintained at a 6-month follow-up. Overall, this study aims to generate highly novel multimodal data on the psychological and biological implications of working time reduction, including observed changes in health, wellbeing, and performance.

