### Participants and inclusion criteria

2.1

The study protocol was approved by the Brighton and Sussex Medical School Research Governance and Ethics Committee (RGEC; protocols ER/BSMS6337/4 and ER/BSMS6337/6) and conducted in accordance with the ethical standards set by the British Psychological Society and the Declaration of Helsinki. The study recruits two groups of participants: those undergoing working time reduction and control participants who do not change working hours.

We aim to recruit a balanced sample of at least 150 participants for all measures (with approximately half who reduce their working time and half controls). Sample size was determined using a power calculation in G^*^Power on questionnaire pilot data (*n* = 30) with an effect size of 0.45, alpha of 0.05 and power of 0.95. This suggests a group sample size of at least 68 is required. Furthermore, participation in certain study components is voluntary (e.g., MRI, blood sample, interoception, sleep, and time-use diaries), and therefore sample sizes are expected to vary across modalities as a consequence of participant self-selection and differential uptake of specific measures; accordingly, statistical power is also expected to vary between outcome domains. However, as this is the first working time reduction trial to use non-self-report measures, it was not possible to estimate power calculations beyond questionnaire data. In addition, as we will not examine moderating subgroup effects within the control group, fewer controls may be required. The primary purpose of the control group is to account for factors unrelated to the intervention itself, including practice effects, familiarity with the MRI scanning environment, and temporal changes that may occur irrespective of working time reduction. This will allow us to determine whether observed changes in outcomes can be attributed to the working time reduction intervention rather than repeated testing or assessment effects.

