### Model design

3.2

This study uses a longitudinal mixed-effects design with a hierarchical structure. Repeated measures data are nested within employees, who are nested within companies, meaning observations are not independent and will be analyzed using multilevel methods. The design includes one between-subjects factor (group: intervention and control) and one within-subjects factor (time, which will vary per analysis with three datapoint options: baseline and end of trial; baseline, end of trial and 6-month follow-up; and the weekly questionnaires), with an interaction between time and group and corrections for multiple tests. When relevant, employee-level (e.g., age, household income) and company-level (e.g., industry, company size) covariates will be added to statistical models. Table 1 provides a list of all planned covariates. The independent variables will be fixed effects, with up to three random effects: time, employee, and organization. Covariates will be added to the model as fixed effects. This design enables us to determine whether changes are observed across time points for the working time reduction intervention group but not for controls.

**Table 1 T1:** Planned individual-level and company-level covariates for inclusion in statistical models.

Category	Covariate	Type
Individual-level	Baseline value of dependent variable	Continuous
	Gender or sex	Categorical
	Household income	Categorical
	Education level	Categorical
	Age	Continuous
	Living area	Continuous
	Job title	Categorical
	Hours of working time reduction	Continuous
	Remote work status	Categorical
Company-level	Industry	Categorical
	Company size	Categorical
	Trial start month	Categorical
	Profit status	Categorical

The specific coding scheme used for categorical variables alongside any data specific covariates will be specified in future modality-specific preregistrations.

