In line with other working time reduction trials, we will include all participants allocated to the intervention group in the primary analyses regardless of the actual extent of their working time reduction, unless the company average reduction of working hours is < 1 h per week. In which case, their data will be excluded from the main analyses. In secondary analyses, we will investigate whether intervention effects vary by the extent of working time reduction by adding this as a moderator in the mixed-effects models. The extent of working time reduction will be calculated as the difference between participants' self-reported weekly working hours before the trial and during the trial. Working time reduction will firstly be modeled as a continuous variable (hours reduced), but we will also explore potential non-linear relationships using categorical hourly brackets. Additional secondary analyses will investigate whether other individual characteristics moderate the intervention effects, such as sex, age, and baseline score for a given measure. Each potential moderator will be evaluated separately by including the relevant interaction terms in mixed-effects models.

Due to the range of data types and the number of variables, variable-specific hypotheses and model variations (i.e., specific moderators and additional covariates) will be addressed in multiple follow-up preregistrations on the Open Science Framework (OSF). These will provide further details on each data-type analysis within the OSF project repository.

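### Part-time staff may enter the primary questionnaire analysis, but the covariate list has no starting full-time status or pre-trial hours, although employers choose their own group

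*Protocol article*

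**What the plan says.** - **Who answers the questionnaires.** Section 2.2 offers them to all staff of participating organisations, "regardless of their original working schedule (e.g., part-time status, compressed hours, etc".), and concludes that "everyone, regardless of working pattern, completes the questionnaires". The remote and in-person measures (Sections 2.9 and 2.10) are offered only to staff who are full-time at the start; the reason given is limited resources.
- **Who is analysed.** Section 3.2: "we will include all participants allocated to the intervention group in the primary analyses regardless of the actual extent of their working time reduction". The one exception is a company whose average cut is under 1 h per week. There is no rule at the level of the individual.
- **What is adjusted for.** Section 3.2: "Table 1 provides a list of all planned covariates". The table holds the baseline outcome, demographic items, job title, hours of working time reduction, remote work status and four company items. Full-time status, contracted hours and pre-trial weekly hours are absent.
- **How groups arise.** Under Section 2.3 a senior decision-maker at each employer chooses the group. Section 2.3 also says that controls are matched on size and sector, not on working pattern. The Discussion acknowledges self-selection and the bias that it can bring.
- **Sample size.** Section 2.1: "We aim to recruit a balanced sample of at least 150 participants for all measures". The Abstract adds further people, "with additional participants completing questionnaires only".

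**The concern.** Hours worked are the exposure under study. The Introduction separates working time reduction from part-time and compressed-hours work, cites benefits that grow with the size of the cut, and links longer hours to poorer sleep and mental health. Starting hours are thus a plausible predictor of how an outcome moves over 12 weeks and of how much a person gains from a cut. In a comparison that is not randomised, such a variable belongs among the common covariates.

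Two things are at stake. First, if the share of part-time staff differs between the groups and their outcomes drift differently, that difference is read as an intervention effect. Second, the all-staff questionnaire effect is an average that may include people with a small cut. It would then be set beside sleep, blood and MRI effects estimated in full-time staff only. The article does not say what reduction part-time staff receive. The adherence item in Section 2.8.2 asks about a work-free day under a 4-day week or 9-day fortnight, and Section 2.8.6 asks leaders for typical hours of full-time staff only.

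**Working it through.** **1. The plan's own figure.** Section 2.1 sizes the study "with an effect size of 0.45, alpha of 0.05 and power of 0.95" and states: "This suggests a group sample size of at least 68 is required". The metric of 0.45 is not named. A two-sided paired t-test with a standardised change of 0.45 needs n = 67 (power at 68 is 0.955), so 68 is reproduced closely on that reading. Read instead as a difference between two independent groups, 0.45 needs 130 per group, and 75 per group gives power 0.78. That gap is a separate matter; the two-group reading is used below only because the primary question is a group contrast.

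**2. What the group-by-time contrast estimates.** Let pT and pC be the part-time shares in the reduction and control groups, gF and gP the change that full-time and part-time staff would show without any cut, e the effect in full-time staff, and r the effect in part-time staff relative to e. Then:

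- mean change, reduction group = (1 − pT)(gF + e) + pT(gP + r·e)
- mean change, control group = (1 − pC)gF + pC·gP
- difference = e·[1 − pT(1 − r)] + (pT − pC)(gP − gF)

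The first term is dilution; it vanishes if r = 1. The second is confounding by starting pattern; it vanishes if the shares are equal or the drifts are equal. For example, a share gap of 20 percentage points passes one fifth of the difference in drift into the estimate. None of pT, pC, r, gF or gP is in the article.

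**3. Range for dilution (assumed p and r, with e = 0.45 and unchanged SD).** The diluted effect is 0.45·[1 − p(1 − r)]:

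| p | r = 0 | r = 0.5 | r = 0.8 |
|---|---|---|---|
| 10% | 0.405 | 0.428 | 0.441 |
| 20% | 0.360 | 0.405 | 0.432 |
| 30% | 0.315 | 0.383 | 0.423 |

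**4. Why no power loss can be claimed.** Power is for a two-sided two-sample t-test, alpha 0.05, without clustering; the reference is 0.78. It depends on whether part-time staff replace full-time staff within 75 per group or come on top of them, so that n = 75/(1 − p), i.e. 83, 94 or 107 per group:

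| p | r | within 75 | on top of 75 |
|---|---|---|---|
| 10% | 0 | 0.69 | 0.74 |
| 20% | 0 | 0.59 | 0.69 |
| 30% | 0 | 0.48 | 0.63 |
| 10% | 0.5 | 0.74 | 0.78 |
| 20% | 0.5 | 0.69 | 0.79 |
| 30% | 0.5 | 0.64 | 0.80 |
| 10% | 0.8 | 0.77 | 0.81 |
| 20% | 0.8 | 0.75 | 0.84 |
| 30% | 0.8 | 0.73 | 0.87 |

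The target of 150 is for all measures, which part-time staff cannot complete, and the Abstract mentions extra questionnaire-only participants. The right-hand column is therefore at least as natural a reading. Even the sign of the change in power depends on figures that are not given.

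**5. Whether an existing covariate fills the gap.** Hours of working time reduction is measured after the start, is near zero by design in controls, and cannot tell a part-time from a full-time employee with the same cut. The baseline outcome removes stable differences in level, but not different changes over time, which are what the second term in step 2 carries.

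**The case against.** Analysing everyone allocated is a declared choice, in line with other trials in this field, and is a legitimate estimand. Section 3.2 leaves data-specific covariates and further moderators to later preregistrations. The Discussion names job control and self-efficacy as covariates although Table 1 omits them, so the list is not closed in practice. Companies with a negligible average cut are excluded, and hours reduced is a secondary moderator. Section 2.1 defines the group as people undergoing a reduction, and Section 2.2 discloses the eligibility difference with its reason. Biological measures are voluntary, so even a full-time questionnaire sample would not match those volunteers exactly.

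Much of this stands. The all-staff primary analysis is not an error, and a preregistration could still add the covariate. But starting pattern bears on every questionnaire outcome, so it belongs in the common list. A company average cannot show whose hours were left uncut, and hours reduced does not replace starting hours.

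A reader might infer three stronger things that the article does not support:

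- **That the effect is diluted and power is lost.** This needs a share and a relative response that are not given. Nothing says that part-time staff receive no cut.
- **That compressed-hours staff have the same problem.** The Introduction defines compressed hours as the same hours in fewer days. Such staff may be full-time and eligible for every measure.
- **That linking questionnaire and biological data within a person mixes populations.** Anyone with both kinds of data was full-time at the start by eligibility. The mismatch arises when group-level effects are compared across data types.

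**Conclusion.** The point holds as a gap in adjustment and interpretation. As written, the plan lets part-time staff into the primary questionnaire analysis and leaves their starting pattern out of the planned covariates, in a comparison where employers choose the group. The group-by-time estimate may be confounded by starting hours, and may be diluted if part-time staff receive a smaller cut or respond less. No single size can be given. With assumed shares of 10% to 30%, an effect of 0.45 in full-time staff would appear as anything from 0.315 (no response in part-time staff, 30% share) to 0.45 (equal response), before any confounding. No statement on power follows. The clear difference in population from the biological measures concerns part-time staff.

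**What to change.** - **Covariate.** Add full-time or part-time status at enrolment to Table 1, with its interaction with time. Status already has to be established to decide eligibility under Section 2.2. Pre-trial weekly hours, collected under Section 2.8.5, are the alternative, with the weakness that they are recalled at the end of the trial.
- **Moderator.** Add working pattern to the secondary moderators as a group-by-time-by-status term. Status by time adjusts for different drift but does not undo dilution of the group-by-time effect; the three-way term or a restricted analysis is needed for that.
- **Sensitivity analysis.** Report a full-time-only contrast beside the all-staff primary result, and cite it when questionnaire group effects are compared with sleep, blood or MRI effects.
- **Reporting.** Give the part-time share and mean reduction by group, so that readers can judge the size of the issue.

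The cost is one more covariate and a smaller n in the full-time contrast. Data collection is expected to end in 2027, so this can still be fixed in the questionnaire preregistration.

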### Recruitment

2.3

Employers have been recruited on a rolling basis between 2022 and 2026. Unlike most national cohort-based working-time-reduction trials, this protocol requires local recruitment because several core measures, including MRI scans, blood samples, and interoception measures, must be conducted in person at the University of Sussex. As only a minority of staff at each organization volunteer for in-person testing, a large pool of local employers is needed to achieve adequate sample sizes on these measures. Therefore, we prioritize organizations based near the research site, and invite them to join the trial at a time that suits their operational needs. Recruitment for both control and working time reduction participants is supported through local business newsletters, community talks by the senior researcher ([name]), public engagement events, research participation bulletins, social media posts, and word of mouth. A small number of employers participating in UK national pilots coordinated by the 4 Day Week Foundation have also opted into the protocol, alongside the national programmes.

Employers are primarily contacted through a senior decision-maker (e.g., CEO, Managing Director, or Human Resources lead), who determines whether their staff will implement working-time reduction or serve as controls. Except for one organization that contributed to both groups, all employees within a given organization are assigned to the same group. Organization leaders inform staff about the study and, where applicable, the planned reduction in working time. Staff are invited to a discovery call with the senior researcher, after which they can opt into the study and select which components they wish to complete (i.e., questionnaires only, additional remote measures, or an in-person visit). Participation in the research is voluntary and independent of eligibility to take part in time management training (see Section 2.5) and, for the working time reduction group, participating in their employer's working time reduction trial.

Most participating organizations are small- or medium-sized enterprises or micro businesses, consistent with other recent working-time-reduction trials (e.g., Fan et al., 2025). A small number of participants take part independently, rather than being recruited as part of an employer, including self-employed individuals. Control organizations are intentionally matched on size and sector, although precise pair-matching is not feasible due to geographical constraints. As recruitment relies on proximity to the research site, the final sample will represent a convenience sample rather than a stratified one. However, a range of sectors are represented in both groups, which will be fully reported in the respective data analysis papers.

### Compensation

2.4

Participants in both the working time reduction and control groups are equally compensated for their time. All participants complete the self-report questionnaires and are offered £50 for their participation (with a minimum completion threshold of 80% of questionnaires for reimbursement). Missed questionnaires are excused in cases of annual leave or sick leave for which we have been informed. Each additional measure is reimbursed separately (£10 for sleep watch and/or time-use diary, £5 for blood sample, £10 for interoception measures, £25 for MRI).

As an additional incentive, we provide anonymised company-level reports to the business with summary results from the wellbeing and workplace questionnaires: baseline vs. end of trial, as well as changes across the weeks for their weekly questionnaires (see Section 2.8 for a summary of these measures). We also offer personalized reports for individual participants on their data from the same measures. For those who undergo an MRI brain scan, we provide an image of their brain. As an incentive for additional time completing the 6-month follow-up, companies and/or individuals can receive an updated report with 6-month follow-up data. No additional participant reimbursement is given at 6-month follow-up.

### Time management training

2.5

Organizations undertaking working time reduction typically undergo work reorganization to accommodate the shorter working week and maintain or improve performance (Fan et al., 2025; Pang, 2023). As part of the research programme, participants are offered a time management training session during the baseline period (before working time reduction commences).

Our team designed this training to mirror that offered to organizations in recent cohort working time reduction trials. The 4 Day Week Global trials offered webinars to help organizations undergo work reorganization, in which low- and zero-value activities, such as unnecessary meetings, are reduced (Fan et al., 2025). The training in the present protocol is a 1-h focus group activity, in which participants receive a short presentation on time management strategies, such as task prioritization, meeting etiquette, and messaging habits. Staff are then asked to reflect on their current time use, identify areas of inefficiency, and develop strategies for work reorganization to use during the trial.

The session is led by the senior researcher ([name]) and delivered online or in person, according to the organisation's preference. For larger companies, multiple sessions are hosted to accommodate more participants while keeping individual session sizes conducive to a workshop (maximum eight participants per session). We offer time management training to both working time reduction and control groups, enabling investigation of the unique effects of working time reduction (which may include increased motivation to use time-management strategies and reorganize work), beyond merely receiving time-management advice.

### Data acquisition and protocol overview

2.6

The research protocol runs for 14 weeks, during which participants complete weekly questionnaires. In the first two baseline weeks, participants maintain their existing working patterns. At baseline, all participants complete wellbeing and workplace questionnaires, and additional remote or in-person measures if chosen. Over the subsequent 12 weeks, participants in the working time reduction group implement their planned reduction in working time, while those in the control group do not change working time. During the final 3 weeks, initial assessments conducted during the baseline period are repeated, alongside additional work patterns and questionnaires for business leaders. We also include an optional 6-month follow-up that repeats the baseline questionnaires. A summary of the protocol is shown in Figure 1. The section below provides details of all assessments used.

